# A Mobile Phone App Intervention to Promote Healthy Salt Intake Among Adults: Protocol for a Randomized Controlled Study

**DOI:** 10.2196/37853

**Published:** 2022-06-29

**Keywords:** mHealth, intervention, sodium chloride, dietary, behavior change, mobile health

## Abstract

**Background:**

There is sound evidence associating high salt intake and a greater risk of cardiovascular and noncardiovascular diseases. High salt intake has been observed in several populations worldwide. Therefore, promoting healthier salt consumption has been encouraged as a low-cost strategy to reduce this risk factor. However, these strategies need to be sound, built on theoretical and methodological bases, and consider the target population’s context.

**Objective:**

This protocol aims to describe a mobile phone app intervention to promote healthy salt intake among adults.

**Methods:**

This is an experimental and longitudinal study protocol conducted in three modules. Module 1 refers to the planning of the intervention based on the Behaviour Change Wheel framework. Module 2 is the development of the mobile phone app intervention based on the date of module 1. In module 3, the intervention will be evaluated using a randomized controlled study, with three steps of data collection in a 2-month follow-up in a sample of 86 adults (43 participants for each group: the control group and intervention group) recruited from the primary health care centers of a Brazilian town. The discretionary salt intake questionnaire will assess salt consumption, the app usability will be assessed using the System Usability Scale, and psychosocial variables (habit, intention, and self-efficacy) will also be measured.

**Results:**

Recruitment began in October 2021, and the follow-up will end in August 2022. The results of this study are expected to be published in 2023.

**Conclusions:**

Results from this study will help people to control salt intake when cooking at home, will stimulate self-care, will work as an alternative or supportive method in the relationship between health care professionals and patients, and will contribute to implementing the app intervention to promote healthy salt intake on a large scale.

**Trial Registration:**

The Brazilian Clinical Trials Registry RBR-4s8qyyq; https://ensaiosclinicos.gov.br/rg/RBR-4s8qyyq

**International Registered Report Identifier (IRRID):**

DERR1-10.2196/37853

## Introduction

It is estimated that salt consumption is high worldwide [1,2], and there is sufficient evidence to associate high salt intake with the development and worsening of cardiovascular diseases [3-7]. A population-based study in a Brazilian town was conducted to characterize salt intake using biochemical and self-report methods, and according to sociodemographic and clinical variables, and found a mean of salt intake based on a 24-hour urine excretion of 10.5 g/day. Most of the salt is derived from the salt added during cooking [8]. It means consuming more than twice the daily recommendation of salt, which is less than 5 grams per day (2300 milligrams of sodium per day) [9,10], and it is the critical salt consumption behavior that should be reduced.

Plans and guidelines conducted by international and governmental agencies [7,11,12] encourage the promotion of a healthy intake of this nutrient in several countries, but changing people’s behavior is not a simple task for educators, researchers, health professionals, and those responsible for creating and implementing public policy strategies. Isolated educational campaigns or population awareness campaigns are insufficient. On the other hand, the results are effective when we associate behavior change interventions based on theoretical models in promoting healthy salt consumption [12-17].

A global systematic review [12] investigated 22 studies related to the impact of behavior change interventions to reduce salt consumption in the population and found that health education at the population level and awareness-raising interventions can improve salt-related behaviors and reduce their salt intake. In the analysis of the interventions developed based on methodological frameworks or models, all studies have shown success in improving the behavior or reduction of salt intake [12]. Thus, reducing salt intake is not a simple behavior to achieve, requiring more specific initiatives with the aid of consistent and effective methodological frameworks to change people’s dietary patterns [12,18,19].

One of the frameworks used to design a behavior change intervention is the Behaviour Change Wheel (BCW). The BCW is a validated synthesis of 19 frameworks of behavior change linked to a broad model that can be applied to any behavior in any setting [20]. At the center of the BCW is the Capability, Opportunity, Motivation, and Behaviour (COM-B) model, which recognizes that the behavior is a complex interaction of all these components, and its variant, the Theoretical Domains Framework (TDF), which synthesizes key theoretical constructs from the 33 behavior change theories [20]. The components of COM-B and the domains of TDF together give a more detailed diagnosis of the behavioral analysis. The BCW has been applied successfully in intervention development in various health-related contexts, including changing eating behaviors [19].

In addition to using a consistent tool to design the intervention, there is the choice of an appropriate way to deliver this intervention. Given advances in information technology, increasing smartphone users, easy internet access, and the use of mobile apps, health care app-based interventions have become a growing area for the promotion and self-monitoring of users’ health because of their cost-effectiveness by encouraging self-care [21], the flexibility in information delivery, and the breaking down of barriers that have been associated with traditional interactions [22,23].

As a result of a low cost and easy access, behavior change interventions through apps have increased considerably in several areas, such as physical activity–related behaviors [24,25], smoking [26], medication adherence [27,28], and depression [29,30] as well as chronic diseases such as diabetes [31] and asthma [32]. Based on this perspective, we set out to promote healthy salt consumption through the app.

Thus, the objective of this protocol is to describe a randomized pilot study aimed at assessing the efficacy of an app intervention to promote healthy salt intake based on the BCW in a Brazilian population and assessing the usability of the app.

## Methods

This study will be conducted in three modules: (1) intervention development using the BCW, (2) elaboration of the mobile phone app, and (3) evaluation of the intervention (Figure 1).

**Figure 1 figure1:**
[figure not shown]
Intervention flow diagram. BCW: Behaviour Change Wheel; COM-B: Capability, Opportunity, Motivation, and Behaviour; TDF: Theoretical Domains Framework.

### Module 1: Intervention Development Using the BCW

Module 1 will follow the BCW stages: understanding unhealthy salt intake, identifying intervention options, and identifying the content and implementation options of the intervention [20].

#### Stage 1: Understanding Unhealthy Salt Intake

Stage 1 includes four steps: (1) definition of the problem in terms of behavior (unhealthy salt intake), (2) selection of the target behavior, (3) specification of the target behavior, and (4) identification of what needs to change using the TDF [33] and the COM-B model.

Steps 1, 2, and 3 will be developed based on previous studies on salt intake among the Brazilian population [8]. In step 4, the TDF and the COM-B model, proposed by Michie and collaborators [20], will be used to identify the behavioral determinants targeted by the intervention. The TDF is an integrative framework developed from a synthesis of psychological theories to provide a comprehensive approach to identifying determinants of behavior [33].

#### Stage 2: Identifying Intervention Options

The first step is called intervention functions. From these functions, it is possible to assess which of these types of intervention give the best results and may be able to change the behavior. The intervention functions will be selected after identifying TDF and COM-B components. There are nine functions described in the BCW: (1) education, (2) persuasion, (3) incentivization, (4) coercion, (5) training, (6) restriction, (7) environmental restructuring, (8) modeling, and (9) enablement.

After selecting functions, we will apply the Affordability, Practicability, Effectiveness/cost-effectiveness, Acceptability, Side-effects/safety, Equity (APEASE) criteria that is used for designing and evaluating interventions [20]. In our study, the APEASE criteria will be by an experts committee formed by two professionals with experience in theories of behavior change, development, and implementation of the intervention; a research professional with knowledge of the BCW guide; a clinician with experience in patient counseling for salt consumption; and a researcher with knowledge of salt consumption and behavior change techniques (BCTs) [34].

The next step in this stage is the policy categories. This step refers to the inclusion of policy makers in the implementation and execution of an intervention. This step is optional. Due to the difficulty of contacting these policy makers in the research development region, they will not participate in this study.

#### Stage 3: Identifying Content and Implementation Options of the Intervention

In stage 3, BCTs and the mode of delivery of the intervention are defined.

In step 1, after identifying the intervention functions, the expert committee will determine the most appropriate BCTs based on the intervention functions selected in stage 2. A BCT is an “observable, replicable, and irreducible component of an intervention designed to change behavior and a postulated active ingredient within the intervention” [20]. This step also requires the application of the APEASE criteria to select the BCTs that will be used in the intervention.

The last step corresponds to the mode of delivery. Driven by recent advances in the use of mobile apps and their use as a health promotion tool delivering beneficial results to users in many areas [24-32] and the current scenario of a pandemic caused by SARS-CoV-2, in which it is necessary to socially distance, we will choose to use the mobile phone app as a remote administration mode. For this choice, a delivery taxonomy was consulted [20].

### Module 2: Mobile Phone App Development

Module 2 aims to develop the mobile phone app, which requires data collection from participants who are potential users of the app.

#### Study Design

To develop the mobile phone app, we will conduct an exploratory study aiming at assessing the needs and preferences of potential users regarding the use of an app for reducing salt.

Potential users will be interviewed to assess their preferences regarding receiving the intervention by the app in an attempt to absorb this empirical reality, which is continually changing, either due to sociocultural diversity, epidemiological dynamics, or technological changes [35].

#### Participants and Recruitment

Potential users were defined as any person interested in using an app for reducing salt. To be eligible, they should be aged between 20 and 59 years (classification of the Brazilian Institute of Geography [36] for adults, the same age group used in a previous study to choose the target behavior), speak Portuguese, have a mobile phone that supports mobile apps, have skill in handling a cell phone, and consent to participate in the study.

Participants will be recruited from a primary health center in an urban Brazilian town, Artur Nogueira, with 56,247 inhabitants, located in a metropolitan region of Sao Paulo, Brazil [36]. A research assistant will be present in the waiting room of the Basic Health unit of the clinical site to meet patients and offer them the opportunity to participate in the project.

#### Data Collection

We will conduct semistructured interviews with potential users to explore participants’ needs (eg, content) regarding the mobile app, their preferences (eg, features and settings) regarding the mobile app, their current use (if any) of or search for health care apps, and their perception of an app for controlling and monitoring salt addition in meal preparation, as we are proposing.

At the beginning of the interview, each participant will be invited to sign a consent form. The interviews will last 30 to 45 minutes and will be recorded.

#### Sample Size

The interviews will be conducted with a convenience sample of potential users of the app. According to Guest and collaborators [37], data saturation occurred within the first 12 interviews. Considering this, we planned to collect data from at least 12 participants while ensuring data saturation.

#### Data Analysis

Audios will be recorded in transcripts and used to extract the information related to factors cited in the Data Collection section and any other relevant information from the interviews. The extracted data will be processed and used to guide the following mobile app development phase.

#### Procedure for Mobile Phone App Development

The mobile app will be developed based on the previous phases/steps and qualitative exploration. We will follow the guidelines for describing health interventions using mobile phones (the mHealth evidence reporting and assessment checklist [38]). The app will be developed by a software engineer using the Android operating system, and it will be written in JavaScript using the React Native framework. After its elaboration, the mobile app will be evaluated by experts to assess its content and layout.

### Module 3: Implementation and Evaluation of the Intervention

#### Study Design

To evaluate the efficacy of the intervention, we will conduct a randomized controlled study, with three waves of data collection in a 2-month follow-up. The SPIRIT (Standard Protocol Items: Recommendations for Interventional Trials) guideline was followed in the description of this module.

#### Eligibility Criteria

The study population is adults living in a Brazilian town (described in module 2). To be eligible to participate in this study, they should be aged between 20 and 59 years, have access to a mobile phone that supports the mobile app, speak Portuguese, and consent to participate in the study.

#### Sample Size and Recruitment

According to the quantitative outcomes, the sample size was calculated considering the objective of comparing the two groups (control group [CG] and intervention group [IG]) in the three periods of time. The methodology of a sample calculation for a repeated-measures ANOVA model was considered to perform this calculation. In this calculation, a significance level of 5%, a test power of 80%, and an effect size of 0.25 were assumed, which, according to Cohen [39], can be considered a medium degree effect size. The first calculation resulted in a sample of 86 participants, but a 20% rate for possible losses was considered, which resulted in a sample of 108 participants (54 participants per group).

Recruitment will occur in primary health care centers of a Brazilian town, with the help of the community health agent of the unit that is linked to each resident of its microarea; the individual will be approached and will invite a resident at home who meets the inclusion criteria to participate in the study. Participants will be selected in a randomized way and will be divided between groups (IG and CG), considering a randomization scheme by blocks of random size. The randomization scheme was generated online [40].

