#### Data Analysis

Qualitative data will be described using frequencies and percentages, and quantitative data as measures of central tendency (mean and median) and dispersion (SD, maximum, and minimum). Correlation tests (Spearman or Pearson coefficient) will test the relation between habit and self-efficacy with intention at T0. Regression analysis using generalized linear models will be used to verify if habit, self-efficacy, and intention at T0 predict the discretionary salt questionnaire at T1 and T2.

To evaluate the efficacy of the intervention, comparisons between groups and times about the discretionary salt questionnaire will be performed using a linear regression model via generalized estimating equations modeling [45].

A significance level of 5% will be adopted. Statistical analyses will be performed using SAS, version 9.4 (SAS Institute).

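### The 80% power behind 86 participants fits a group effect averaged over baseline and follow-up, so it does not carry over to the efficacy comparison

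*Protocol article*

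**What the plan says.** Under Sample Size and Recruitment (Module 3), the objective that was sized is given as "considering the objective of comparing the two groups (control group [CG] and intervention group [IG]) in the three periods of time". The method is stated: "The methodology of a sample calculation for a repeated-measures ANOVA model was considered to perform this calculation". For the inputs, "a significance level of 5%, a test power of 80%, and an effect size of 0.25 were assumed", and the effect size, it says, "can be considered a medium degree effect size". The result follows: "The first calculation resulted in a sample of 86 participants". The number is then raised to 108 to allow for 20% losses. The section does not say whether the effect tested is the group main effect or the group-by-time interaction, and it gives no correlation between repeated measurements.

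Under Data Collection (Module 3), T0, T1 and T2 are one month apart. The salt questionnaire is first completed at T0, the visit at which the app is installed.

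Under Data Analysis (Module 3), the efficacy analysis is described thus: "comparisons between groups and times about the discretionary salt questionnaire will be performed using a linear regression model via generalized estimating equations modeling".

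**The concern.** A repeated-measures calculation with two groups and three waves can refer to several tests, and the sample size differs greatly between them. If 86 belongs to the group difference averaged over all three waves, one of those waves is a pre-intervention baseline at which randomisation makes the expected difference zero. Including it dilutes any effect that appears at T1 and T2. The pairing of 80% power with a medium effect would then describe a quantity that does not answer the efficacy question. A later reader of a null result would attach the 80% to whichever contrast was reported, although it was not calculated for that contrast.

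**Working it through.** **Inputs from the article.** Two groups, allocated 1:1 ("43 participants for each group: the control group and intervention group"); m = 3 waves; significance level 5%; power 80%; Cohen's f = 0.25, which for two groups is d = 2f = 0.5.

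**Assumptions.** The article gives no correlation between waves. I use ρ = 0.5, equal between all pairs of waves, and show 0.3 to 0.7. Powers use the noncentral F distribution with complete data and equal variances, as an approximation to the GEE model.

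**Step 1: reproduce 86.** For the between-group main effect, λ = N f² m / [1 + (m − 1)ρ], with 1 and N − 2 degrees of freedom.
- N = 86: λ = 86 × 0.0625 × 3 / 2 = 8.06, power 80.1%.
- N = 84: power 79.2%.

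So 86 is the smallest even N that reaches 80%. The match depends on ρ: the required N is 70 at ρ = 0.3 and 104 at ρ = 0.7, and lies within 2 of 86 for ρ from 0.46 to 0.52.

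**Step 2: try the alternatives with the same f.**
- Group-by-time interaction, λ = N f² m / (1 − ρ): N = 28 at ρ = 0.5, and 54 at ρ = 0.
- Interaction with λ = N f², (N − 2) f² or (N − 2)(m − 1) f²: N = 156, 158 and 82.
- Comparison at a single wave: N = 128.

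None of these gives 86.

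**Step 3: allow for T0 being baseline.** With d = 0 at T0 and d = 0.5 at T1 and T2, the average is (0 + 0.5 + 0.5)/3 = 0.333, so f = 0.167. At N = 86 and ρ = 0.5, λ = 86 × (1/6)² × 3 / 2 = 3.58, and power is 46.5% (47.3% by normal approximation). It is 55% at ρ = 0.3 and 40% at ρ = 0.7. Over the correlations that come within 2 of 86 (0.46 to 0.52) it is 48.0% to 45.7%.

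Conversely, an average of d = 0.5 needs a post-baseline difference x with 2x/3 = 0.5, so x = 0.75.

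**Step 4: contrasts that could serve the efficacy comparison.** N = 86 (43 per group), differences (0, 0.5, 0.5), ρ = 0.5. For the single-contrast rows, the noncentrality is 0.5² / (2v/43), where v is the variance in units of the single-wave variance.

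| Contrast | Variance or λ | Power |
|---|---|---|
| Group-by-time, 2 df | λ = (43/2) × (1/6) / 0.5 = 7.17 | 66% |
| T2, unadjusted | v = 1 | 63% |
| T2, adjusted for T0 | v = 1 − ρ² = 0.75 | 75% |
| Mean of T1 and T2, adjusted for T0 | v = (1 + ρ)/2 − ρ² = 0.50 | 90% |

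For the 2-df row, 1/6 is the sum of squared deviations of (0, 0.5, 0.5) from their mean. The last row is 86% at ρ = 0.3 and 97% at ρ = 0.7.

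**Step 5: loss allowance.** 86 / (1 − 0.20) = 107.5, rounded up to 108. This is correct.

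**The case against.** **The article never says that the main effect was sized.** True. That reading is inferred from the match with 86 and needs an assumed correlation. The inference is strong, because no other standard form tried returns 86, but it remains an inference.

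**If f = 0.25 is simply the size of the tested effect, 80% is correct.** Also true. But with a baseline wave in the average, that effect is d of about 0.75 at each follow-up wave, and the article calls the input medium. Either the label or the power has to give way.

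**The correlation and the exact GEE contrast may be in a fuller document.** They may, and their absence from an article is not the point here. The point is that a stated power, effect size and sample size do not describe the efficacy comparison.

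Three stronger readings are tempting, and the document supports none of them.
- A reader might infer that the trial has 47% power. That figure belongs only to the averaged main effect. The article plans a GEE comparison of groups and times and nowhere makes the averaged difference the deciding test.
- A reader might infer that the trial is too small. The T0-adjusted mean of T1 and T2 has about 90% power with the same 86 participants.
- A reader might infer a calculation error. Both 86 and 108 reproduce.

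**Conclusion.** The point holds as a mismatch between the effect that was sized and the efficacy question. Read as the averaged main effect, the calculation has 80% power only if the post-baseline effect is d of about 0.75. For d = 0.5 at T1 and T2 that test has about 47% power (55% to 40% for correlations 0.3 to 0.7). The stated 80% matches none of the four efficacy contrasts checked, whose power is 63% to 90% at correlation 0.5.

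This rests on the inferred main effect, an equal correlation of 0.5, 86 complete participants, and an effect fully present by T1. The last assumption matters: if d is 0.25 at T1 and 0.5 at T2, power for the T0-adjusted mean of T1 and T2 falls to 68%, while the T2 contrasts keep their 63% and 75%. The contrast therefore has to be named before any power figure means much.

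**What to change.** Rewrite the sample size paragraph around the contrast that will decide efficacy:
- Name a post-baseline contrast within the GEE model, for example the between-group difference in the mean of T1 and T2, adjusted for T0. Other post-baseline contrasts are defensible; the choice should reflect when the effect is expected, and should be made before outcomes are seen by group.
- State the assumed correlation between waves and the standardised difference at each follow-up wave.
- Restate the power of 86 analysable participants for that contrast. For the example with d = 0.5 at both waves, this is about 90% at correlation 0.5, and 86% to 97% for correlations 0.3 to 0.7.
- If the averaged main effect is kept, give its detectable post-baseline effect as d of about 0.75 and drop the description of that effect as medium.

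The cost is one paragraph, with a matching sentence under Data Analysis. The allowance to 108 stands, and no extra participants are needed.
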